**Table 2: Mental (MDI) and Psychomotor (PDI) Development indices of Mexican full term infants**

| **Age**  **(mo)** | **n** | **MDI**  *Mean + S.D.* | **PDI**  *Mean +* *S.D.* |
| --- | --- | --- | --- |
| 1 | 113 | 99.15 + 5.22 | 99.55 + 7.80 |
| 3 | 112 | 98.29 + 5.20 | 98.15 + 7.20 |
| 6 | 102 | 99.46 + 6.03 | 97.04 + 9.18 |
| 12 | 97 | 101.12 + 9.01 | 93.59 + 9.33 |

[name] and her group evaluated visual acuity using the Acuity Teller Cards procedure. Total n-6 and n-3 fatty acids as well as the n6:n3 ratio in maternal RBC were the best predictors of better visual acuity scores; infant visual acuity at 3 months of age was also positively and significantly associated with maternal RBC levels of adrenic acid, AA/EPA ratio and AA/DHA ratio after adjusting for birth weight, length at birth and breast-feeding, but not with maternal dietary PUFA intakes*[[159]](#endnote-159)*. A study of brainstem auditory evoked potentials at one month of age detected a negative linear relationship between maternal RBC levels during last trimester of pregnancy and the latency intervals, suggesting that higher maternal levels of DHA and AA were associated with improved conduction times between the auditory stimulus and the cochlear nucleus. In addition, preliminary results also showed that exclusively breast-fed infants who had higher intakes of DHA had higher mental (7 points) and motor (3 points) development scores using the BSID-II at 12 months of age. In addition to the observational studies described above, [name] is starting an intervention trial in a public hospital in Mexico that will examine the impact of supplementing formula fed infants with LCPUFAs (DHA and AA) on infant growth, immune response and neurodevelopment using brain stem auditory and visual evoked potentials.

**[name]** is an Emory psychologist interested in the role of maternal depression and child-care giving for young child growth and development. *As part of a NIH funded study, she has recently completed data collection in collaboration with INSP* to test the hypothesis that caregivers who report higher levels of distress, stress, and lower levels of perceived social support will exhibit more negative interactions and caregiving behavior, which will in turn be associated with poorer growth, development, and nutritional status in young children. Interviews were conducted with the child's primary caregiver when the child is 9 and 15 months of age to assess levels of depressive symptoms, parenting stress, and perceived social support. Other measurements include in-home observations of caregiver-child interactions at 9 and 15 months, and child growth and development at 18 and 24 months of age that were collected as part of the larger micronutrient supplementation study (PI: [name]). *Preliminary results suggest that many women (46.5%) are experiencing high levels of depressive symptoms (46.5%) and stress related to child caregiving.[[160]](#endnote-160). Analyses examining relationships between caregiver stress/distress, caregiver-child interactions, and child growth and development are currently underway. [name] is also involved in analyses of data from the larger* *micronutrient study and preliminary results show that both lower birth weight and length, and poor weight gain from birth to nine months predict poorer motor development[[161]](#endnote-161),[[162]](#endnote-162).* Her expertise in measuring maternal competence and child development especially with the Spanish version of the latest version of the Bayley Scales of Infant Development (BSID-II) will be invaluable for the proposed study.

**D. RESEARCH DESIGN AND METHODS: *(revised)***

**D.1. Research Design** *(revised)*

##### **D.1.1. Study Hypotheses** *(added specific hypothesis 3c)*

The ***central hypothesis*** is that DHA supplementation during pregnancy will improve child growth and development during infancy, and will be tested by conducting a randomized double-blinded placebo-controlled trial in Mexico.

The **specific hypotheses** are:

- 1. Compared to those who receive a placebo, women who receive DHA supplements during the latter half of pregnancy will have **higher DHA concentrations in breast milk and blood** at 1 and 3 months post-partum.

2. Compared to those born to women who receive a placebo, infants born to women who receive DHA supplements during the latter half of pregnancy will have **improved birth outcomes** as follows,

a. Greater birth weight and length and longer gestational age

b. Better neurodevelopmental indicators (Apgar and Neonatal Behavioral Assessment Scale scores)

1. Increased cord blood levels of polyunsaturated fatty acids.
2. Compared to those born to women who receive a placebo, infants born to women who receive DHA supplements during the latter half of pregnancy will have **better growth and neurodevelopment during the first 18 months of life**, namely

a. Increased weight, length and head circumference at 1, 3, 6, 9, 12 and 18 months of age

- 1. Higher Neonatal Behavioral Assessment Scale scores at 1 month of age
  2. *Improved visual and brainstem auditory evoked potentials at 1 month of age*
  3. Improved visual recognition and attention at 6 and 12 months of age
  4. Higher global motor and mental development scores at 6, 12 and 18 months of age
  5. Increased postnatal growth rates independent of birth size
  6. Higher global motor and mental development scores at 18 months of age independent of differences observed at earlier time points (e.g. 6 and 12 months).

1. Compared to those born to women who receive a placebo, infants born to women who receive DHA supplements during the latter half of pregnancy will **higher DHA concentrations in blood** at 3, 12 and 18 months of age.

**D.1.2. Study Design** *(revised)*

A **randomized controlled double blind trial** will be used to test the hypothesis whether prenatal supplementation with DHA improves child growth and development. Pregnant women will be recruited at 20 weeks of gestation and will be randomly allocated to either the intervention group (daily supplements during pregnancy of 200 mg of DHA) or to the control group (a placebo that is similar in appearance and taste). The commercial preparation Neoformins PLTM produced by Martek will be used. Each tablet provides 200 mg DHA synthesized from an algae source which is safer and more acceptable than the fish oils that have been used in earlier studiesError: Reference source not found,Error: Reference source not found,Error: Reference source not found. The rationale for this dosage is that it represents a physiological dose that is safe and will meet the minimum recommended intake of 300 mg/d in combination with dietary sources that are expected based on our preliminary data to contribute about 100 mg/d. *Recent studies have shown that a dose of 200 mg of DHA is as effective as higher doses in improving DHA status during pregnancyError: Reference source not found,Error: Reference source not found,Error: Reference source not found and lactationError: Reference source not found and more importantly that 200 mg of DHA is safe. Studies that have used only DHA, whether from algal sources or as DHA enriched eggs, did not find any adverse effectsError: Reference source not found,Error: Reference source not found,Error: Reference source not found. In the only study in which a tendency for increased bleeding was reportedError: Reference source not found the supplement was from marine sources and contained substantially higher amounts of DHA (nearly 2000 mg of DHA; about 10 times our proposed dose) and more importantly, high amounts of EPAError: Reference source not found. A dose of 200 mg is safe and can be provided in one pill, which would help ensure compliance. Finally if found effective, a dose of 200 mg of DHA is amenable to safe and feasible dietary recommendations for pregnant women to increase their DHA intakes using food based approaches, such as increasing the frequency of consumption of fatty fish, use of DHA enriched foods such as eggs and routine consumption of supplement.* The placebo will be similar in appearance, taste and composition to the treatment, except for DHA. Random allocation of all eligible pregnancies to either the treatment or control group will be done using a computer- generated list to be created by the study biostatistician at Emory based on an allocation ratio of 1:1 without blocking constraints[[188]](#endnote-188). All study subjects and members of the study team will be blinded to the treatment code, which will be maintained in sealed envelopes at INSP and RSPH, and opened only at the end of the study and data analysis, or made available to the external data safety monitoring committee if requested (see section E).

The inclusion and exclusion criteria for study subjects are as follows:

**Inclusion criteria**

- 20-24 weeks pregnant (based on last menstrual period)
- 18 - 35 years old
- Resident of Cuernavaca who intends to deliver at the IMSS General Hospital I and remain in the area for the next 2 years
- Intends to predominantly breastfeed infant until 3 months of age
- Agrees to participate with informed consent

**Exclusion criteria**

- High risk pregnancy: This will be as documented in the clinical record at recruitment and will include history and prevalence of abruptio placentae, any serious bleeding episode in the current pregnancy, gestational diabetes, pregnancy induced hypertension, maternal toxoplasmosis infection during pregnancy, coagulation disorders, thrombocytopenia or chronic vascular, renal or systemic disease and drug use.
- Lipid metabolism (hyperlipidemia) and/or absorption disorders
- Regular intake of fish oil or DHA supplements during pregnancy
- Chronic use of medication for illnesses like epilepsy

Informed consent will be obtained from all subjects following standard procedures (see section E) and women will be free to withdraw voluntarily at any time. All study protocols will be explained to the study subjects and will be approved by the Human Investigations Committees at Emory University and INSP. Supplements packaged in blister packs, will be delivered at home weekly by trained field workers who will also monitor compliance by interview and pill count. *Preliminary data collected from women (n=49) who had recently delivered at the IMSS Hospital in Mexico City revealed that most of them (87.5%) considered weekly supplementation at home desirable and  not invasive. Recent data from the National Nutrition Survey in Mexico have shown that only 13.8% of pregnant women reported consuming any micronutrient supplements[[189]](#endnote-189) in contrast to the high coverage rates (> 80%) that we achieved in our clinical trials in Xoxocotla with daily or weekly home visitsError: Reference source not found.* All subjects will have access to routine prenatal care. Infants will also have access to standard care and will be followed up until 18 months of age. The total duration of follow-up will therefore be 23 months for each mother-child pair.

The rationale for repeated measures of growth and development during the first 18 months of life is that frequent measurements until a later time point will more likely provide more accurate information on the dynamic process of infant growth and cognitive development. An advance attributed to the growing theoretical shift in the field of developmental psychology states that measuring the developmental course of cognitive function in infancy should be conducted within the realm of developmental systems theory[[190]](#endnote-190). Therefore, we will conduct more extensive longitudinal measurements and use measures of the developmental course of variables assessing whether nutritional supplementation affects cognitive outcome. The second methodological implication of the broader, developmental systems approach is that we will consider whether variables other than LCPUFA manipulations interact with the manipulations themselves. For example, it is possible that LCPUFA supplementation has larger effects in populations in which environmental quality (e.g., socioeconomic status or caregiver responsiveness) is poor, compared with populations in which environmental conditions are more optimal. A third implication is that small or transient effects at one age point may not be unimportant. The fact that there may be no differences in, for example, visual acuity at 6 months ignores the possibility that the acceleration of the visual acuity curve experienced by the supplemented group may have a longer-term effect. Thus, even a small early advantage in lower-order function may serve to affect higher-order functions at some later point. Further, in infancy the developmental process itself complicates the measurement of developmental functioning. For example, the Bayley may measure motor development well at 12 months, but be less valid for language development at this age as these skills are just emerging, or may be a predictor of intelligence at 24, but not at 6 months. There is also some evidence that among low-risk infants, scores within the first year of life are not predictive of later IQ, but those after 18-24 months provide more useful predictions; however, the instrument may be more predictive even within the first year of life among high-risk infants[[191]](#endnote-191). Similarly, growth faltering begins during the latter half of infancy and often continues through the second year of life. Although later prediction is not the main purpose of this study, the inclusion of these measurements will help our understanding of the underlying processes.

**D.1.3. Study Site:** *(no changes)*

This study will be carried out at the IMSS General Hospital I located in the city of Cuernavaca, Morelos, Mexico. The IMSS General Hospital I had over 9,000 women registering for prenatal care and about 3,189 deliveries in 2000. About one-third had their first visit during the first trimester, and about 60% had their first prenatal visit before week 20. The women who usually attend the hospital are medium-low socioeconomic status and either they and/or their husbands are employed. In most cases, the patient usually pays a third of the health care costs, with the Federal Government and their employer paying the other two-thirds (one third each). All pregnant women are routinely provided with tetanus toxoid vaccination and iron-folate supplementation (5 mg/day of folic acid and 100 mg of iron fumarate or sulfate) during pregnancy. Routine prenatal care will be provided by registered physicians (graduated from the Gynecological Residency) who will be assisted by registered nurses and residents. Mothers are given appointments for prenatal checkups beginning with the diagnosis of the pregnancy for each month during the 1st and 2nd trimester, and during the third trimester, every 2 weeks and during the last month, each week.  Coverage at each of these routine prenatal visits is about 70%. After birth, infants come to the hospital for monthly well baby visits in the first year of life during which they receive routine immunization and monitoring of growth and development. Infant length and weight is measured and mothers are counseled by trained nurses in a range of topics that include family planning, breast feeding, nutrition, and child development. These visits become bimonthly in the second year of life. Coverage rates for immunization are very high (>95%) for the various vaccines, and about 75% for the routine monthly visits for infants. Almost all mothers initiate breast feeding and about 60% are still predominantly breast feeding at 3 months post partum.

**D.1.4. Sample Size and Power Calculations:** *(no changes)*

**Table 3: Expected effect sizes for key study outcomes at birth and during the postnatal period**

| **Study Outcomes** | **Birth** | | | **Postnatal (3-18 mo)** | | |
| --- | --- | --- | --- | --- | --- | --- |
|  | ***S.D.*** | ***Minimum difference (d)*** | ***Effect Size*** | ***S.D*** | ***Minimum difference (d)*** | ***Effect Size*** |
| **GrowthError: Reference source not found** |  |  |  |  |  |  |
| Weight (kg) | 0.45 | 0.1 | **0.22** | 1.0 | 0.3 | **0.30** |
| Length (cm) | 1.6 | 0.5 | **0.31** | 3.0 | 1.0 | **0.33** |
| Head Circumference (cm) | 2.0 | 0.5 | **0.25** | 1.5 | 0.5 | **0.33** |
| Gestational Age (d) | 7.0 | 2.0 | **0.29** | - | - | **-** |
| **Development Error: Reference source not found***.****Error: Reference source not found*** |  |  |  |  |  |  |
| Brazelton Score | 1.0 | 0.8 | **0.80** | - | - | **-** |
| Fagan Test | - | - | **-** | 2.7 | 2.00 | **0.74** |
| Mental Development Index | - | - | **-** | 15 | 3.75 | **0.25** |
| Motor Development Index | - | - | **-** | 15 | 3.75 | **0.25** |
| **DHA statusError: Reference source not found*,Error: Reference source not found*** |  |  |  |  |  |  |
| Maternal blood***** | 1.0 | 0.50 | **0.5** | 1.0 | 0.50 | **0.50** |
| Infant blood***** | 1.0 | 0.50 | **0.5** | 1.0 | 0.50 | **0.50** |
| Breast milk (% TFA) | **-** | **-** | **-** | 0.08 | 0.04 | **0.50** |

**plasma phospholipid DHA levels expressed as % total fatty acids (TFA)*

Sample size calculations are based on the expected effect size, power to detect those differences and level of significance. The expected effect sizes for key outcomes presented in Table 3 were calculated by dividing the minimum meaningful difference (d) that we wish to detect by the standard deviation (S.D.) using data from either the literature or from our preliminary studies in Mexico and Guatemala. Most of the effect sizes are small to medium (0.2 to 0.5) and the minimum sample sizes required to detect them using a two-tailed test and confidence level of 0.05 are shown in Table 4 at different levels of power (80-95%)[[192]](#endnote-192). The smallest effect sizes of interest are 0.22 S.D. for birth weight and 0.25 S.D. for motor and mental development at 18 months of age. Using a two tailed test and a significance level of =0.05, a final sample of 338 infants per group at the end of the study will have 90% power to detect an effect size of 0.25 S.D. or greater for all the major outcomes. This sample size will have 80% power to detect meaningful differences in birth weight (0.22 S.D) as we expect at least 393 births/group after accounting for loss to follow-up (see section D 1.5). The power calculations are also presented for single outcomes as well as for repeated measures of growth and development assuming correlations of 0.2. Due to budgetary constraints, blood and breast-milk samples will be obtained for a 30% sub-sample of 120 mother-infant pairs per group, which will have 95% power to detect expected effect sizes of 0.5 S.D.

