**Table 4: Minimum sample sizes by effect sizes, power and number of measurements**

| **Effect**  **size** | **Minimum Sample size per Group (2 tailed test, alpha=0.05, Correlation between repeated measurements=0.2)** | | | |
| --- | --- | --- | --- | --- |
| 80% Power  Time Points  1 2 3 | 85% Power  Time Points  1 2 3 | 90% Power  Time Points  1 2 3 | 95% Power  Time Points  1 2 3 |
| 0.2 | 393 237 185 | 450 271 211 | 526 317 247 | 651 391 305 |
| 0.3 | 175 106 83 | 201 121 95 | 234 142 110 | 290 175 136 |
| 0.4 | 99 60 47 | 113 69 54 | 132 80 63 | 163 99 77 |
| 0.5 | 64 39 31 | 73 45 35 | 85 52 41 | 105 64 50 |

**D.1.5. Recruitment of study subjects**: *(revised)*

*The power calculations dictate that a* minimum of 676 mother-child pairs should complete the study. We expect a 15% loss to follow up during pregnancy and a further 20% loss in infancy, and therefore need to recruit at least 994 pregnancies. *These estimates are conservative and include losses due to deaths and migrations out of the study area. All efforts however will be made to keep losses to a minimum. Attendance at routine prenatal and postnatal visits is already high in our study hospital and in addition we will be providing incentives to encourage participation.* Recent data indicate that IMSS General Hospital I has approximately 250 births/month, of which ~60% are predominantly breastfed until 3 months of age. The proportion of pregnancies that are high risk and therefore ineligible for inclusion is about 10%. Based on the above data, we expect to recruit at least 100 eligible pregnancies per month and therefore to complete recruitment in 10 months. The 30% subsample of mother-infant pairs for biochemical determinations will be selected at random.

**D.1.6. Time line:** *(revised)*

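### The birth-weight power sentence in D.1.4 attaches the sample size for 0.20 SD to an effect of 0.22 SD: 393 births per group give about 87% power there, so the stated 80% is conservative (minor)

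*Protocol*

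**What the plan says.** Table 3 gives the birth-weight inputs in kilograms as SD, minimum difference and effect size: "Weight (kg) | 0.45 | 0.1 | 0.22". Section D.1.4 sets the test with "Using a two tailed test and a significance level of =0.05", and section D.1.2 describes randomisation as "based on an allocation ratio of 1:1 without blocking constraints".

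D.1.4 then makes two power statements. The first, with its effect in SD units, sizes the trial: "a final sample of 338 infants per group at the end of the study will have 90% power to detect an effect size of 0.25". The second concerns birth weight: "This sample size will have 80% power to detect meaningful differences in birth weight (0.22 S.D) as we expect at least 393 births/group". It says that this number allows for losses and refers to section D.1.5.

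Table 4 has rows for 0.2, 0.3, 0.4 and 0.5 SD and none for 0.22. The 80% power entries of its first row, for one, two and three time points, read "0.2 | 393 237 185".

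Section D.1.5 plans for at least 676 completing pairs and at least 994 recruited pregnancies, assuming "a 15% loss to follow up during pregnancy and a further 20% loss in infancy".

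**The concern.** A power statement has four linked parts: the test, the number per group, the effect size and the power. Once three are fixed, so is the fourth. Here the test, the 393 and the 0.22 SD are all stated, and the power they imply is not the stated 80%. The figure 393 is recognisable as the Table 4 entry for a different effect size.

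D.4.2 lists birth weight among the principal outcomes, and D.1.4 names 0.22 SD as the smallest effect of interest. A reader will therefore use this sentence to judge the trial's sensitivity to a 100 g difference. As written, it gives a type II error of 20% at that difference, where the sentence's own births figure implies about 13%. The sentence also cites D.1.5 for the number of births, and D.1.5 does not produce that number.

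**Working it through.** **Inputs.** Two-sided alpha 0.05 (D.1.4). 1:1 allocation (D.1.2). Birth-weight SD 0.45 kg and difference 0.1 kg, so 0.1 / 0.45 = 0.222, shown as 0.22 (Table 3). 338 per group at the end (D.1.4). 994 recruited, 676 completing, losses of 15% and then 20% (D.1.5). The comparison is taken as an unadjusted two-sample comparison of means, since D.4.2 names Student's t test for weight.

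**Formulas.** For n per group and standardised effect d:
- power = Phi( d x sqrt(n / 2) - 1.96 )
- n = 2 x (1.96 + 0.8416)^2 / d^2 for 80% power

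Each result was also checked with the non-central t distribution.

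**Step 1: reproduce the plan's other figures.**
- 338 per group at 0.25 SD: 0.25 x sqrt(169) = 3.25; 3.25 - 1.96 = 1.29; power 90.2% (t: 90.1%). Agrees with the stated 90%.
- 393 per group at 0.20 SD: 0.20 x sqrt(196.5) = 2.804; 2.804 - 1.96 = 0.844; power 80.1% (t: 80.0%). Agrees with Table 4.
- Recruitment: 676 / (0.85 x 0.80) = 994. Agrees with D.1.5.

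**Step 2: the birth-weight sentence.**
- 393 per group at 0.22 SD: 0.22 x sqrt(196.5) = 3.084; 3.084 - 1.96 = 1.124; power 87.0% (t: 86.9%). With the unrounded 0.222 SD it is 87.6% (t: 87.5%). The stated 80% is not reproduced.
- Needed for 80% at 0.22 SD: 2 x 7.849 / 0.0484 = 324.3, so 325 per group (t: 326).
- 338 per group at 0.22 SD: 0.22 x 13 = 2.86; 2.86 - 1.96 = 0.90; power 81.6% (t: 81.5%).

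**Step 3: births per group from D.1.5.**
- 994 x 0.85 / 2 = 422. Working back from completers, 338 / 0.80 = 422.5.
- Cross-check: D.2.1 expects about 85 births a month from about 100 recruited. Over the 10 months of recruitment that is about 850, or 425 per group.
- 422 per group at 0.22 SD: 0.22 x sqrt(211) = 3.196; 3.196 - 1.96 = 1.236; power 89.2% (t: 89.1%).
- No loss rate in D.1.5 yields 393. The 15% gives 422, and both losses together give 338. The 20% alone gives 994 x 0.80 / 2 = 398, and that rate applies after birth.

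| Births per group | Source | Power at 0.22 SD |
|---|---|---|
| 338 | completers, D.1.4 | about 82% |
| 393 | floor, D.1.4; Table 4 row for 0.20 SD | about 87% |
| 422 | 994 x 0.85 / 2, D.1.5 | about 89% |

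**The case against.** The best defence is that the sentence is true as a lower bound. Table 4 is a coarse grid of minimum sample sizes. For 0.22 SD the nearest safe row is 0.2, which asks for 393 at 80% power. Expecting at least that many births guarantees at least 80% at the larger effect. It can also be said that the sentence refers back to the 338 per group named just before it, for which 80% is about right. Both arguments have weight, and they are why the statement is better called mismatched and conservative than wrong in its direction. They do not remove the mismatch. The sentence rests its 80% on the births, and if 338 alone were the basis, the births clause would not be needed.

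Three stronger readings are tempting, and the protocol does not support them.

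- *The births figure contradicts D.1.5 and implies a 21% loss in pregnancy.* The arithmetic behind this is 1 - 786/994 = 0.21. But the text gives 393 as a floor, and 422 lies above it. No 21% loss is stated or implied. What can be said is that 393 is not derived from D.1.5. A floor below 422 is also sensible. In the investigators' earlier micronutrient trial, birth weight was available for 639 of 656 pregnancies with birth outcomes (97.4%). Assuming the same rate here, 0.974 x 422 = 411 per group, which gives about 88% power.
- *The detectable difference is really 87 g.* At 422 per group, 80% power is indeed reached at 0.193 SD, and 0.193 x 0.45 kg is about 87 g. But the 100 g in Table 3 is a minimum meaningful difference set without reference to the number of births, and it does not shrink as births increase.
- *The sentence would distort how a null birth-weight result is read.* Such a result is read from its estimate and confidence interval, not from a planned power figure.

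**Conclusion.** The point holds as a mismatch within one sentence. The 393 per group belongs to 0.20 SD at 80% power. Attached to 0.22 SD it gives about 87%, so the stated power is some 7 percentage points too low. On the births that D.1.5 leads to, about 422 per group, power is about 89%. These figures assume a two-sided 5% comparison of two means, 1:1 allocation, and the Table 3 SD of 0.45 kg.

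The error is on the safe side. Enrolment of 994 comes from 338 per group at 0.25 SD with 90% power and the two loss rates, and that chain reproduces. Neither the size of the trial nor any analysis depends on the birth-weight sentence. Severity is minor.

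**What to change.** Replace the birth-weight sentence in D.1.4 with one of these:

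- *About 422 births per group are expected (994 x 0.85 / 2), giving about 89% power for 0.22 SD (100 g).*
- If 393 is kept as a cautious floor, for example to allow for births without a measured weight: *At least 393 births per group give about 87% power for 0.22 SD (80% for 0.20 SD).* The sentence should then say that 393 is a floor set below the roughly 422 births that follow from D.1.5.

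The cost is one sentence. The 100 g minimum meaningful difference, the recruitment target and the analysis stay as they are.
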